#### Exercise intervention

While there are no guidelines for the delivery of exercise in cancer survivors, it is recommended to follow the guidelines for general UK population [25]. Hence participants randomised to the exercise intervention in this study will be advised to carry out the programme for at least 50 min three times per week.

The exercise programme includes elements of aerobic, upper and lower limb resistance training, core stability and stretches and is designed to be performed independently at home. For the aerobic component, participants will be advised to walk indoors or outdoors for a minimum of 30 min and to aim for moderate intensity as recommended by the Borg Rate of Perceived Exertion (RPE) scale [26]. Where unable to maintain moderate intensity due to fatigue, weakness or other complaints, participants will be advised to aim for moderate intensity aerobic exercise for any duration of time able, and to gradually increase over the next few weeks aiming to build up to 150 min over one week. They will be taught resistance exercises for the major upper and lower limb muscles using body weight or TheraBand™ isometric resistance bands to carry out following aerobic activity. The resistance training follows American College of Sports Medicine (ACSM) guidelines [27], and participants will be advised to carry out three sets of each exercise for 8–12 repetitions. They will also be taught stretches for upper and lower limb muscles, and core abdominal exercises in supine. Participants will be also be provided with written instruction, leaflet with photographs and advice sheet. Similar programmes incorporating aerobic, resistance and flexibility training three times a week over a twelve week period have been used with good results in improving QoL in cancer survivors [9].

#### Relaxation intervention

The relaxation intervention consists of a bed- or chair-based program, developed based on the literature on mindfulness-based interventions in cancer survivors [10–12]. An audio CD was produced to guide participants through relaxation techniques incorporating mindfulness meditation, breathing exercises, guided visualisation and progressive muscle relaxation. Here also participants will be advised to carry out the programme for 50 min three times a week. Participants will also be provided with written information on relaxation and tips on how to incorporate into daily life. Participants in this group will not be advised to perform any exercise outside of their normal habits, nor asked to avoid activity.

Participants will be followed-up at six weeks, midway through the programme. At this stage all assessments will be repeated, any change noted and they will be advised on how to modify the programme (relaxation or exercise) as appropriate. Once participants have completed twelve weeks of their intervention, they will be provided with resources of the other intervention group, for their information or to carry out as desired, in accordance with the Declaration of Helsinki.

### Outcome measures

All outcome measures will be assessed at baseline prior to commencing intervention, midway (six weeks) and on completion of intervention programme (twelve weeks). Outcome measures, instruments and guidelines used and time assessed are summarised in Table 1. At baseline, patient demographics including gender, age, social history and medical history will be recorded.

**Table 1 Tab1:** Primary and Secondary Outcome Measures

Outcome measured	Instrument	Guidelines	When assessed		
			Baseline	Midway 6 weeks	End of intervention 12 weeks
Primary outcome					
Quality of Life	EORTC QLQ-C30	Self-reported Questionnaire	☑	☑	☑
Secondary outcomes					
Body Composition	Height, Weight, Bioimpedance analysis – BMI, Body Fat % - TANITA BC-418 Body Composition Analyzer	Same investigator and equipment, time of day and clothing kept similar where possible	☑	☑	☑
Cardiovascular status – Resting BP, HR, SpO2	Omron M10-IT electronic BP monitor, Solaris Finger Pulse Oximeter S10A		☑	☑	☑
Pulmonary Function – FEV1, FVC, FER, PEF	Hand-held Micro 1 Medical Microspirometer	British Thoracic Society, 2013	☑	☑	☑
Muscle Strength – Grip Strength	Jamar® Hydraulic Hand Dynamometer	American College of Sports Medicine, 2014	☑	☑	☑
Functional Exercise Capacity	Six Minute Walk Test	American Thoracic Society, 2002	☑	☑	☑
Physical Well-being, Social/Family Well-being, Emotional Well-being, Functional Well-being	FACT-Lym	Self-reported Questionnaire	☑	☑	☑
Anxiety and Depression	HADS		☑	☑	☑
Feelings and Perceptions about participating in programme	End of Study Questionnaire	Open-ended Questionnaire mailed to participants’ home			☑

#### Quality of life

The primary outcome measure is QoL, assessed by the EORTC QLQ-C30. This self-reported questionnaire has been demonstrated to be a valid and reliable tool, takes approximately eleven minutes to complete and most subjects require no assistance [28]. This has been used extensively in cancer survivorship research, and also specifically with lymphoma patients [29]. The EORTC QLQ-C30 consists of thirty items. Each question is answered on a four-point scale and scores are derived according to the EORTC scoring manual [30].

#### Body composition

Due to the illness itself and treatment and side-effects (including steroid use, loss of appetite, nausea and vomiting), lymphoma patients may experience a fluctuation in weight and body fat percentage during the duration of their treatment. Therefore body composition will be assessed using a bioelectrical impedance analyser (Tanita BC-418) to monitor whether it will stabilise to within the desired range. Participants’ standing stature will be measured using a stadiometer (SECA, Germany). Height measured will be inserted into the body composition analyser to obtain weight, body mass index (BMI), and body fat percentage. Participants will be measured without footwear and in light clothing using the same equipment each time.

#### Cardiovascular and pulmonary status

Resting Blood Pressure (BP) and Heart Rate (HR) will be assessed using an electronic BP monitor (Omron M10-IT, Japan) and finger pulse oximeter (Solaris S10A, China) in sitting. In addition, measures of pulmonary capacity and function will be assessed using a hand-held microspirometer (Micro 1 Medical Microspirometer, England) following British Thoracic Society guidelines [31]. Forced expiratory volume in one second (FEV1), forced vital capacity (FVC), forced expiratory ratio (FER) and expiratory peak flow (PEF) will be recorded.

#### Muscle strength

Grip strength is a good indication of global muscle strength and assessment of grip is common method that is used to assess general strength characteristics [32]. Here, isometric grip strength will be measured in kilograms using an adjustable hand-held dynamometer (Jamar***®*** Hydraulic Hand Dynamometer, USA) with the elbow flexed at 90 degrees and the forearm and wrist in neutral position following standardised American College of Sports Medicine (ACSM) guidelines [32].

#### Functional exercise capacity

Due to the variation in the population being studied in terms of age, co-morbidity and physical ability, a submaximal test was considered appropriate for this study. The Six-Minute Walk Test (6MWT) is considered a good indicator of functional ability and exercise capacity and is a common outcome measure to evaluate progress in rehabilitation programmes [33]. This test was chosen as it can be undertaken in a clinical setting with ease, takes a short duration of time to complete and appeared appropriate for this sample of patients following chemotherapy who are generally deconditioned and fatigue quickly. The 6MWT has been validated and used extensively in a variety of patient populations, and has been recommended for use in cancer patients also [34].

The 6MWT will be carried out following guidelines recommended by the American Thoracic Society (ATS) [33]. The test will be carried out in a 30 m marked distance, and the total distance covered in 6 min will be recorded, as well as post-test Heart Rate and oxygen saturation, RPE and Rate of Dyspnoea [26]. The test will cease prior to 6 min if the patient chooses to stop or the tester terminates testing (indications for terminating exercise as per the ATS guidelines include the following: severe exhaustion or shortness of breath, wheezing, dizziness, chest pain or muscle cramps) [33]. At no point will the patient be encouraged to continue beyond the level at which they wish to stop.

#### Well-being

The Functional Assessment of Chronic Illness Therapy (FACIT) questionnaires have been validated in studies of cancer management and are designed to encompass a range of psychosocial factors [35]. Like the EORTC QLQ-C30, these questionnaires are also a patient reported measure of QoL. However these questionnaires focus on aspects of well-being including physical, social, emotional and functional well-being subscales. Here, the lymphoma-specific scale (FACT-Lym) will be used (comprising the general or FACT-G questionnaire plus a lymphoma subscale. The FACT-Lym has good internal consistency and validity [35]. All questions are answered on a five-point scale and scoring guidelines are recommended together with the questionnaire [36].

#### Psychological status

The Hospital Anxiety and Depression Scale (HADS) is a valid tool for assessing the severity of anxiety disorders and depression in various populations including psychiatric, primary care patients and the general population [37]. The HADS is also recommended in cancer settings [38]. Questions are answered using a four-point scale and higher scores represent higher levels of anxiety and depression.

#### End of study questionnaire

During their final assessment at twelve weeks, participants will be invited to complete the end of study questionnaire. The open questions aim to explore their thoughts and feelings about the intervention programme, and to analyse their views on their particular intervention including preferences, perceived advantages and disadvantages and reasons for participation and adherence.

### Data analysis

Data will be entered into the Microsoft Excel (2013) database by SH and analysed by all authors using the IBM SPSS version 22 (SPSS, Inc., Chicago, IL) statistical software package. The intent-to-treat principle will be applied and the significance level will be set at 0.05. Descriptive statistics will be used to present baseline demographic characteristics. To compare difference in the primary outcome measure, QoL score between the two groups post-intervention, ANCOVA (analysis of covariance) will be used, with pre-test values as covariate to adjust for any baseline differences. Data will be analysed to check fit for ANCOVA assumptions. Post-hoc paired-samples t-tests for pre-post intervention will be tested within groups with Bonferroni corrections. Missing data will be treated as recommended by scoring guidelines of questionnaires [24, 30]. These analyses will be repeated for secondary outcome measures, providing data fit normal distribution and other assumptions for ANCOVA. The influence of potential confounding factors such as age, gender, number of co-morbidities and ECOG status will be explored using correlation analyses. Adherence and drop-out rates will also be analysed. Qualitative data from the end of study questionnaire will be analysed for codes and themes using qualitative content analysis [39].

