### Interventions

Interventions for this study are reported using the template for intervention description and replication (TIDieR) checklist and guide [24].

For both groups, advice, instruction, demonstration and practice will be carried out at baseline. This will be delivered by the principal investigator SH, an experienced physiotherapist with a special interest and experience in oncology. Participants will be able to contact SH by telephone in between sessions if additional support is required. All participants will be advised on potential adverse events and what to report including pain, fatigue, muscle soreness, lymphoedema, nausea, dyspnoea, dizziness, tachycardia and cramp. A logbook will be provided to all participants to encourage adherence and document self-reported participation levels, intervention type carried out, frequency, intensity, duration and any adverse events.

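### Intention-to-treat is stated, but a two-time-point ANCOVA with only a questionnaire-scoring rule for missing data leaves no place for participants without a 12-week score, and the 6-week scores go unused

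*Protocol article*

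**What the plan says.** The Data analysis section of the protocol article makes three statements that bear on this point.

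- Principle: "The intent-to-treat principle will be applied and the significance level will be set at 0.05".
- Primary model: for the "QoL score between the two groups post-intervention, ANCOVA (analysis of covariance) will be used", "with pre-test values as covariate to adjust for any baseline differences". This is one outcome time and one covariate.
- Missing data: "Missing data will be treated as recommended by scoring guidelines of questionnaires [24, 30". No other missing-data rule is printed.

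The same analyses are to be repeated for the secondary outcomes. Drop-out is foreseen, but the section plans only to analyse its rate.

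On timing, the Outcome measures section says: "All outcome measures will be assessed at baseline prior to commencing intervention, midway (six weeks) and on completion of intervention programme (twelve weeks". Table 1 confirms a 6-week assessment for every quantitative outcome. The only use given for it, under Relaxation intervention, is to note change and advise on modifying the programme.

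On the two references, the Quality of life section says that "scores are derived according to the EORTC scoring manual [30", so reference 30 is a scoring manual. The Interventions section identifies reference 24 as the "template for intervention description and replication (TIDieR) checklist and guide [24". The FACT-Lym scoring reference, under Well-being, is 36.

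**The concern.** Taken together, the stated model and the stated rule do not deliver the stated principle. An ANCOVA with a single follow-up cannot include a participant who has no follow-up score. A rule for scoring questionnaires has nothing to act on when no questionnaire came back, and it has no meaning for the physical measures.

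What is at stake is the between-group comparison. People may leave an exercise programme and a relaxation programme for different reasons. If leaving depends on how they were doing at week 6, and does so differently in the two arms, the participants who remain are no longer comparable. The baseline score corrects only part of that. The 6-week score carries more of the information, and it will already be in the database.

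**Working it through.** **1. The text.** Take a participant assessed at baseline and week 6 who then leaves. The ANCOVA needs a 12-week value and has none. The printed rule concerns questionnaire scoring. No imputation, repeated-measures model or definition of the intention-to-treat set for this participant is printed. The participant therefore contributes nothing, and the 6-week score is not used.

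**2. An SD for illustration.** The Sample size section gives 23 per group, two-sided 0.05, 80% power and a difference of 5 to 10 points, but no numerical SD. Solving backwards:

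- Normal approximation: standardised difference = (1.960 + 0.842) × √(2/23) = 0.826.
- t-test: 0.845.
- Implied SD for 10 points: 10/0.845 = 11.8 to 10/0.826 = 12.1. For 5 points it would be 5.9 to 6.0.

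The figure of 46 can thus be matched only by choosing the SD. I use 11.8 as an assumption.

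**3. Simulation.** All of the following are assumptions:

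- SD 11.8; correlations baseline–week 6 0.6, baseline–week 12 0.5, week 6–week 12 0.7.
- 23 per arm, true difference 0.
- About 20% loss after week 6, with a logistic dependence on the 6-week score.
- 6,000 to 8,000 trials per setting.

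Two estimates were compared:

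- Completer ANCOVA: Y12 = b0 + b1·arm + b2·Y0, fitted to those with Y12.
- Likelihood estimate using week 6: fit Y6 = a0 + a1·arm + a2·Y0 to all with Y6, and Y12 = c0 + c1·arm + c2·Y0 + c3·Y6 to completers. The estimate is c1 + c3·a1.

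| Loss after week 6 | ANCOVA bias (points) | ANCOVA type I error | Bias using week 6 |
|---|---|---|---|
| Opposite directions; weak / moderate / strong dependence | 1.0 / 1.7 / 2.4 | 5.6% / 7.8% / 9.6% | at most 0.05 |
| One arm only | 0.5 to 1.2 | about 6% | at most 0.05 |
| Random, or the same in both arms | none | no inflation | none |

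Consistency check: the simulated SD of the ANCOVA estimate is about 3.47. A bias of 1.7 is 1.7/3.47 = 0.49 standard errors, so type I error ≈ Φ(−1.96 + 0.49) + Φ(−1.96 − 0.49) = 0.071 + 0.007 = 7.8%, as simulated.

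The upper row is not a ceiling. With a log-odds slope of 2 per SD in opposite directions, bias was 2.9 points and type I error 13%. A separate one-arm setting (46 participants, SD 12.1, correlations 0.6 to 0.7) gave a bias of 0.9 when the true difference was 0 and 0.6 when it was 10.

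**4. Precision under random loss.** The SD of the estimate was 3.47 for ANCOVA and 3.34 with week 6 at 23 per arm (1 − 3.34/3.47 = 3.7% smaller). At 18 per arm, the abstract's 36 in total, it was 3.91 and 3.80 (2.8% smaller). Across settings the gain was 1 to 4%.

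**5. Where the week-6 score cannot help.** With opposite-direction loss at slope 1, and half of the drop-outs also missing week 6, the likelihood estimate keeps a bias of about 0.7. At slope 2 it keeps about 1.2, against 2.95 for ANCOVA. If all drop-outs miss week 6, the two estimates are identical.

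**The case against.** The best counter-case has five parts.

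- **Exclusion is not stated.** A reader might infer that the plan excludes drop-outs or openly contradicts intention-to-treat. It does neither in words. Intention-to-treat first means analysis by randomised group, and nothing printed departs from that. This stands, and the point is limited accordingly to what follows if the text is applied as it is.
- **An unseen analysis plan may cover it.** The article is condensed, and silence on missed visits would be no fault. This does not dispose of the point, because the article is not silent: it fixes a model and a missing-data rule, and the two do not fit the principle.
- **The content of the scoring manual is not in the documents.** True; that it concerns partly completed forms is a reading of what a scoring manual is for. The physical outcomes do not depend on that reading, since no questionnaire guideline can apply to them.
- **The larger biases are chosen scenarios.** This stands. Opposite-direction selection is the unfavourable case, and the documents give nothing to show it will occur. The simulation also examined bias in a likelihood estimate, not the type I error of the mixed model itself.
- **ANCOVA at the final visit is a standard primary analysis, and week 6 already has a purpose.** Both are true. With few missed visits, ANCOVA would serve well. The case for change is that the data are already collected and the change costs little.

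**Conclusion.** The point holds in a limited form. As printed, the primary ANCOVA and the scoring rule leave participants without a 12-week score outside the analysis, give the physical outcomes no missing-data rule at all, and leave the 6-week scores unused.

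The numerical consequence is conditional on about 20% loss after week 6, an SD near 12 and the assumed correlations. It runs from no bias (random or like loss), through about 0.5 to 1.2 points (selection in one arm), to about 1 to 2.4 points with type I error of about 6 to 10% (opposite directions). The Sample size section treats differences from 5 points as clinically meaningful, so the upper end would matter and the lower end is small.

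Two stronger readings are not supported. One is that the trial's result will be biased by some 2 points: that needs an adverse drop-out pattern for which the documents give no evidence. The other is that a mixed model restores a full intention-to-treat analysis: it does nothing for participants lost before week 6 or for loss that observed scores do not explain.

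The citation of reference 24 as a scoring guideline is a clerical slip and adds no weight.

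**What to change.** - Make the primary analysis a mixed model for repeated measures on the 6- and 12-week scores, with baseline score, treatment, visit, treatment-by-visit and baseline-by-visit, an unstructured covariance and small-sample degrees of freedom such as Satterthwaite.
- Name the treatment contrast at 12 weeks as the primary result, with participants analysed as randomised.
- Keep the 12-week ANCOVA as a sensitivity analysis.
- Restrict the questionnaire scoring rules to missing items within a returned form, and correct the citation from 24 to 36 alongside 30.
- Use the same model for the continuous secondary outcomes, including the physical measures.
- Report, by arm, the number lost before week 6 and between weeks 6 and 12, with reasons, since the model cannot correct for the first group or for loss unrelated to observed scores.

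The cost is a few lines of text and slightly more modelling in a standard procedure. No new data are needed. If loss turns out to be random, nothing is given up and the standard error is 1 to 4% smaller.

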## Discussion

A large proportion of lymphoma survivors continue to experience unmet needs following treatment [1–3]. Long-term and late effects are often overlooked, and survivors do not routinely receive advice or interventions to target these and maximise well-being [40]. Previous studies have supported the use of both relaxation and exercise interventions to treat physical and psychosocial complaints of cancer survivors [9–12]. No trial to date has compared efficacy of these two interventions in lymphoma survivors.

The REIL study aims to study a sample of lymphoma survivors shortly post-chemotherapy, and compare the effectiveness of relaxation and exercise on improving QoL. This study was developed to address some issues highlighted in survivorship literature including focus on survivors of cancers other than breast or prostate, emphasis on the transition phase immediately following treatment, addressing physical, psychological and social needs of lymphoma survivors, use of patient-reported outcome measures, self-management, and moving from control groups to comparison between two interventions.

In this study lymphoma patients in remission will be recruited within six weeks of their last chemotherapy session. Patients during this early phase of survivorship who have completed initial cancer treatment have been relatively neglected [19], and this period immediately following treatment has been identified as a key time to address side effects of treatment and facilitate return to pre-morbid health [41]. Studies on cancer survivors have indicated that they would prefer to begin an exercise programme immediately or soon after treatment [42], and at this point the focus can move from the disease and treatment to ‘moving on’ to the next phase of life [43].

While the additional psychosocial benefits of supervised group classes for cancer survivors have been recognised [44], the need for a shift towards self-management in cancer survivorship has been highlighted [6, 7]. Here participants are supported to self-manage in a variety of ways, but the onus will be on them to initiate contact with the healthcare professionals for additional support when needed [7, 8]. Both the relaxation and exercise programmes in this study are designed to be performed independently and participants will be supplied with resources to allow convenient home-based performance, including written instructions and advice. Participants will be able to contact the investigator whenever required. This study will provide results including adherence and drop-out rates that are more generalizable to ‘real-world’ lymphoma survivors than controlled clinic-based research. Home-exercise programmes also afford patients better scheduling flexibility, familiar surroundings, family support and reduced travel requirements [45].

It will not be possible to stratify participants by factors such as age, gender, etc. during randomization due to the small sample size. However, sample size was calculated using reference values (including standard deviation) and power calculations recommended by the EORTC reference manual [23]; similar trials on the effects of exercise in cancer patients have been carried out with comparable sample sizes, and these were able to detect significant results [9].

In addition to quantitative data from outcome measures, the end of study questionnaire will explore participants’ perceptions and feelings towards an intervention programme post-chemotherapy. Such information will highlight behaviours and patterns in this sample of lymphoma survivors including reasons for participation, adherence and non-adherence, and any preferences; it is anticipated that this data will ultimately help in the promotion of a healthy lifestyle in lymphoma and cancer survivors.

The authors will aim to publish results from this study to add to the evidence to inform healthcare professionals on effective interventions to improve QoL of lymphoma survivors.

